### Intervention

Patients who meet the enrollment criteria will be randomized 1:1 to either the NEO or the SUG group, receiving NEO or SUG as reversal drugs, respectively, in identical volumes and injectors, with other treatments exactly the same. Patients in the NEO group will receive 50 μg kg^−1^ neostigmine and 15 μg kg^−1^ atropine, while those in the SUG group will receive 2 mg·kg^−1^ sugammadex before the end of operation when TOF count (TOFc) ≥ 2. Drug dosing of anesthesia induction, anesthesia maintenance, and reversal will all be dependent on ideal body weight.

#### TOF monitoring

All enrolled patients will undergo neuromuscular monitoring (adductor of pollicis acceleromyography) with ulnar nerve stimulation using the TOF monitoring device (model No. BeneVision N12; Shenzhen Mindray Biomedical Electronics Co, Ltd., Shenzhen, China). Abduce the forearm of the patient and locate two electrodes along the ulnar nerve, with the distal electrode placed at the intersection of the radial margin of flexor carpi ulnar and proximal wrist stripes, and proximal electrode attached at a distance of 3 cm from the distal one. The transducer should be placed on the ipsilateral distal thumb, perpendicular to the direction of its movement. The device will be calibrated, with T4/T1 at 0.95–1.05, using standard TOF methodology after administration of a hypnotic drug and before muscle relaxation. During the operation, the frequency of TOF stimulation will be 2 Hz, and the wave width will be 200 μs, with a measurement interval of 15 min. During the process, the monitored arm should be free to move. TOFr and TOFc before and after antagonism and immediately before extubation will be recorded on the CRF. No further TOF stimulation will be carried out after extubation. We perform TOF monitoring because TOFr > 0.9 is one of the extubation standards, and we want to verify that diaphragm recovery may be still insufficient despite adequate peripheral TOFr.

#### Induction of anesthesia

After entering the operating room (OR), the WHO surgical checklist will be completed, followed by the establishment of intravenous catheterization, three-lead electrocardiogram, non-invasive blood pressure, pulse oximeter, and other necessary monitoring. General anesthesia will be induced with propofol 2 mg kg^−1^, fentanyl 1.5~2 μg kg^−1^, and rocuronium 0.6 mg kg^−1^ as an intravenous bolus. Tracheal intubation will be performed after TOFc declined to 0.

#### Maintenance of anesthesia

Sevoflurane will be supplied at an age-adjusted end-tidal concentration of 1.0 minimum alveolar concentration (MAC) in an air/oxygen mixture. Fentanyl will be titrated with a bolus of 0.5 μg kg^−1^ every 30 min, to keep an adequate level of analgesia. To maintain neuromuscular block, rocuronium will be re-administered when TOFc exceeds 2 with a bolus of 0.2 mg kg^−1^. Mechanical ventilation will be set at 6~8 ml/kg referred to the ideal body weight as tidal volume and 12~15 rates per minute as respiratory rates according to respiratory carbon dioxide ranging from 30 to approximately 40 mmHg. Extubation will be performed when all the following criteria are met: (1) the patient is awake and can execute simple commands, (2) the patient’s respiratory pattern is regular with a tidal volume of 6–7 ml/kg referred to ideal body weight, and (3) the TOFr is > 0.9.

#### Diaphragm ultrasonography

Before induction of anesthesia, 10 min after extubation, and 30 min after extubation, the right hemidiaphragm of the patient will be evaluated by a specially trained and skilled sonographer (an independent anesthesiologist) using a wisonic ultrasound instrument (model No. Compass; Shenzhen Wisonic Medical Technology Co, Ltd., Shenzhen, China). The sonographer was specifically trained in carrying out diaphragm and lung ultrasonography for 3 months. We only observe and evaluate the right hemidiaphragm because the left one is less accessible and reproducible [27]. The enrolled patient will be placed on the bed in a semi-decubitus position, with the head of the bed raised 45°.

DE of the right hemidiaphragm can be explored by a low-frequency US transducer (convex or phased-array probe) placed along the midclavicular line or below the right costal margin, during respiratory maneuvers such as quiet breathing, voluntary sniffing maneuver, and deep inspiration [28]. DE (amplitude in cm, velocity in cm/s especially during sniffing) can be measured using M-mode ultrasonography. The velocity during the sniffing maneuver can be measured from the baseline to the point of maximum height of inspiration, partially reflecting the potential contractility of the diaphragm [29]. On the zone of apposition (ZOA) to the rib cage for the right hemidiaphragm, it is possible to measure the diaphragmatic thickness (DT) with a high-frequency linear array probe [27]. Diaphragmatic TF can thus be calculated as the ratio, thickness at end-inspiration (TFI) − thickness at end-expiration (TEE) divided by TEE [30]. The diaphragm can be distinguished on the graph by identifying the hyperechoic pleural and peritoneal layers, with these two layers enclosing the hypoechoic diaphragmatic muscle. Three uninterrupted and undisturbed respiratory cycles will be measured and averaged for DE or DT/TF.

#### Lung ultrasound

It is reported that LUS may be used as the primary imaging technique to assess PPCs by distinguishing A lines, B lines, and other typical signs, to assess pulmonary conditions and enhance bedside decision making [31, 32]. In this trial, LUS will be performed on subjects also by Mindray ultrasound instrument (model No. Compass; Shenzhen Wisonic Medical Technology Co, Ltd., Shenzhen, China), before induction of anesthesia, 10 min after extubation, and 30 min after extubation, respectively, by the same anesthesiologist specifically trained in carrying out diaphragm and lung ultrasonography for 3 months.

Each hemithorax can be divided into 3 regions with the anterior and posterior axillary lines—anterior, lateral, and posterior—each of which can be divided into upper and lower parts, that is, 6 examination areas of each hemithorax. The scoring system distinguishes four ventilation patterns as follows: normal aeration (score of 0, presence of lung sliding with A lines and up to two isolated B lines), moderate loss of pulmonary ventilation (score of 1, no fewer than 3 dispersive B lines originated from the pleural cavity), severe loss of pulmonary ventilation (score of 2, multiple coalescing B lines), and pulmonary consolidation (score of 3). As a result, the score of the total lung ranges from 0 to 36. The higher the score, the worse the pulmonary condition, and for each region, the worst visible pattern was recorded.

### Outcomes

#### Primary endpoint

The primary outcome will be the incidence of PPCs 30 days after surgery in neostigmine and sugammadex groups. Using conventional broad criteria for diagnosis of PPCs, any postoperative pulmonary abnormality that adversely affects the clinical course of a patient could be defined as a PPC, including acute respiratory distress syndrome (ARDS), atelectasis, bronchospasm, pleural effusion, pneumothorax, respiratory failure, respiratory infection, and various other forms of upper airway obstruction [33–35] (see Table 1 for more details of its definition). The PI will make a phone call on postoperative day 30 (POD30) to retrospectively check whether there have been PPCs after the surgery till now and make a detailed record of the symptoms, severity, and kind of PPCs on the CRFs.

**Table 1 Tab1:** Definition of postoperative pulmonary complications (PPCs) [36]

PPCs	Definition
**Acute respiratory distress syndrome (ARDS)**	Acute onset of hypoxemia (partial pressure of oxygen, arterial (PaO_2_)/fraction of inspired oxygen (FiO_2_) ≤ 300 mmHg) with new bilateral infiltrates in the setting of either a normal pulmonary arterial wedge pressure (PAWP ≤ 18 mmHg) or the absence of suspected of left atrial hypertension when PAWP was not available
**Atelectasis**	Collapse of the alveoli; lung opacification with a shift of the mediastinum, hilum, or hemidiaphragm toward the affected area; and compensatory over inflation in the adjacent non-atelectatic lung
**Bronchospasm**	Newly detected expiratory wheeze treated with bronchodilators
**Pleural effusion**	Chest radiograph demonstrating blunting of the costophrenic angle, evidence of displacement of adjacent anatomical structures, or (in supine position) a hazy opacity in one hemithorax with preserved vascular shadows
**Pneumothorax**	A collection of air in the pleural space (the area with no vascular bed surrounding the visceral pleura)
**Respiratory failure**	Postoperative PaO_2_ 60 mmHg on room air, a PaO_2_/FiO_2_ < 300 mmHg, or arterial oxyhemoglobin saturation measured with pulse oximetry < 90% and requiring oxygen therapy
**Respiratory infection**	Treatment with antibiotics for a respiratory infection, plus at least one of the following criteria: new or changed sputum, new or changed lung opacities, fever, and leukocyte count > 12,000/mm^3^

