## Methods/design

### Study aim

This trial aims to compare the incidence of PORC and PPCs in the sugammadex and neostigmine groups utilizing diaphragm ultrasonography and lung ultrasound and try to conclude whether sugammadex has an advantage over neostigmine in eliminating the occurrence of PORC and PPCs.

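### The only collection step stated for the primary endpoint, a day-30 phone call, cannot by itself establish most Table 1 criteria, and the text leaves room for events outside that table

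*Protocol article*

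**What the plan says.** Under Primary endpoint, the protocol article states: "The primary outcome will be the incidence of PPCs 30 days after surgery in neostigmine and sugammadex groups". It introduces PPCs through a broad concept, that "any postoperative pulmonary abnormality that adversely affects the clinical course of a patient could be defined as a PPC". It then lists seven named conditions plus "various other forms of upper airway obstruction", and refers the reader to Table 1 for the definitions.

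Table 1 has seven rows: ARDS, atelectasis, bronchospasm, pleural effusion, pneumothorax, respiratory failure and respiratory infection. Typical criteria are "Chest radiograph demonstrating blunting of the costophrenic angle" for pleural effusion and, as one limb of respiratory failure, "Postoperative PaO_2_ 60 mmHg on room air". There is no row for upper airway obstruction.

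The same section gives one way of collecting these events: "The PI will make a phone call on postoperative day 30 (POD30) to retrospectively check whether there have been PPCs". The caller records symptoms, severity and kind on the CRF.

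Randomization, allocation, and concealment says that the project leader, who makes this call, keeps the sealed randomization codes and the emergency letters. Blinding is stated there for patients and major anesthetists, and under Statistical analyses for the statistician. It is not stated for whoever assesses the primary outcome.

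**The concern.** Two things do not fit together. First, the definition relies on test results and the stated collection step is a conversation. A call can elicit symptoms and treatments. It cannot by itself establish a PaO2/FiO2 ratio, an opacity, a saturation below 90% or a leukocyte count. Short-lived events in the recovery unit, where an effect of the reversal agent might be expected to show, are among those a patient is least likely to know about a month later.

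Second, the boundary of the endpoint is open. One listed class has no criterion, and the general sentence says that abnormalities could be defined as PPCs without saying whether an event that fits no row counts. That decision falls to the caller.

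At stake is misclassification of the outcome on which the superiority claim rests: defined events missed, undefined events admitted. Because the caller also holds the codes, it cannot be taken for granted that such errors are equal between arms.

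**Working it through.** **Definition against collection (Table 1 and Primary endpoint)**

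| Table 1 row | Rests on | Can a phone call establish it? |
|---|---|---|
| ARDS | PaO2/FiO2, bilateral infiltrates, wedge pressure or no suspected left atrial hypertension | No |
| Atelectasis | Lung opacification with displacement of structures | No |
| Bronchospasm | New wheeze treated with bronchodilators | Partly |
| Pleural effusion | Chest radiograph | No |
| Pneumothorax | Air in the pleural space, in effect an imaging finding | Not by itself |
| Respiratory failure | PaO2, PaO2/FiO2, or oximetry with oxygen therapy | No |
| Respiratory infection | Antibiotics plus sputum, opacities, fever or leukocyte count | Partly (antibiotics with sputum or fever) |
| Upper airway obstruction | No row | No criterion to apply |

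No section shown schedules postoperative chest imaging, blood gases, leukocyte counts, chart review or adjudication for PPCs. Other parameters lists none of these. The Discussion mentions follow-up procedures to 30 days but does not name them.

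**The planned sample size**

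Inputs: 15.4% in the elderly, power 90%, 20% loss and 207 per group (Sample size calculation); significance level 0.05 (Statistical analyses; two-sided is my assumption). The sugammadex rate is not stated. I take it to be the 5% quoted in the same section for all non-cardiac surgery.

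Formula: n = (z₀.₉₇₅ + z₀.₉₀)² × [p₁(1 − p₁) + p₂(1 − p₂)] / (p₁ − p₂)²

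- (1.960 + 1.282)² = 10.507
- 0.154 × 0.846 + 0.05 × 0.95 = 0.17778
- (0.154 − 0.05)² = 0.010816
- n = 10.507 × 0.17778 / 0.010816 = 172.7
- 172.7 × 1.2 = 207.25, that is 207

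The stated 207 is reproduced, which supports 5% as the comparison rate without proving it.

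**Effect of missed events on power**

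Suppose a fraction s of true events is captured, equal in both arms, with no false positives. The observed rates are then 0.154s and 0.05s. Power is the exact binomial probability that the uncorrected chi-square test is significant at 0.05. Two sizes are used: 165 per arm (207 × 0.8 = 165.6, rounded down) and 207 per arm (no loss).

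| Capture s | Observed rates | Power, 165 per arm | Power, 207 per arm |
|---|---|---|---|
| 100% | 15.4% v 5.0% | 0.899 | 0.950 |
| 75% | 11.6% v 3.8% | 0.780 | 0.864 |
| 50% | 7.7% v 2.5% | 0.589 | 0.690 |
| 30% | 4.6% v 1.5% | 0.366 | 0.463 |

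**Adding false positives from an open definition**

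Take 75% capture and 95% specificity, again equal in both arms:

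- neostigmine: 0.75 × 0.154 + 0.05 × 0.846 = 0.158
- sugammadex: 0.75 × 0.05 + 0.05 × 0.95 = 0.085

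Power with 165 per arm is then 0.534. The observed control rate of 15.8% is close to the planned 15.4%, so an observed rate near the planning value would not show that classification was sound.

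The documents give no capture fraction or specificity. All those values are assumptions.

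**The case against.** The strongest reply is that the article never calls the phone call the only source. Figures 1 and 2 and the full protocol are not shown, and chart review is a detail that an article may leave out. A reader might infer that PPCs are collected by the call and nothing else; the documents do not support that. What stands is narrower. For its primary endpoint the article does state a method, and that method does not match the definition printed beside it.

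A reader might also infer that a call can detect nothing in Table 1. That goes too far, since two rows can partly be reported by phone.

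The general sentence can be read as a concept that Table 1 makes operational, and it is limited to abnormalities that affect the clinical course. It is therefore not shown that the plan counts every pulmonary abnormality. The missing row for upper airway obstruction and the permissive wording remain.

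Study aim says the trial will "compare the incidence of PORC and PPCs in the sugammadex and neostigmine groups utilizing diaphragm ultrasonography and lung ultrasound", which might suggest that a recovery-room ultrasound finding counts as a PPC. Other sections largely settle this. The Abstract makes lung ultrasound a secondary outcome, the Background says it cannot replace CT for discerning PPCs, and the Discussion says there is no consensus on diagnosing PPCs by it. Table 1 has no ultrasound criterion.

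Two further inferences are not supported. That the observed rate will differ from 15.4% is not shown: missed and extra events move it in opposite directions, and how the cited studies ascertained PPCs is not visible. A pull of the difference towards zero is not assured either, because it requires equal error in both arms.

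**Conclusion.** The point holds in limited form and should be fixed. The stated collection step cannot by itself establish the imaging, blood-gas, oximetry and leukocyte criteria that define most of the primary endpoint. The text also leaves events outside Table 1 to the judgement of a caller who holds the randomization codes.

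The size depends on how much the call misses, which the documents do not tell us. Relative to about 90% power at full capture with 165 per arm, 75% capture would cost about 12 percentage points and 50% capture about 31. With no loss to follow-up the starting point is 95%, and the corresponding costs are about 9 and 26 points. These figures rest on the inferred 5% sugammadex rate, equal error between arms and perfect specificity. If errors differ between arms, the result could be biased in either direction.

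**What to change.** 1. State that only events meeting a Table 1 row count towards the primary endpoint, and that the general sentence on abnormalities adds none.
2. Give upper airway obstruction a row with a criterion, or remove it from the list.
3. Record in-hospital PPCs up to discharge from existing charts (oximetry, blood gases, imaging, laboratory results, treatments), extracted by study staff blinded to allocation.
4. Use the day-30 call for events after discharge, checked against records where these can be obtained.
5. Add one sentence saying that lung ultrasound findings in the recovery unit do not by themselves count as a PPC.

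If the full protocol already provides for chart review, item 3 reduces to saying so.

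The cost is a modest amount of data extraction. No new tests are needed, and patients already enrolled can be covered from their charts. One limit remains: a Table 1 event for which no test was done in routine care will still be missed, and the documents do not say which tests are routine after arthroplasty.

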#### Secondary endpoints

The secondary outcome will be the incidence of PORC in the two groups 10 min and 30 min after extubation, using diaphragmatic ultrasound as the method of appraisal. TF during a deep breath of 0.36 was considered as the threshold to exclude diaphragm dysfunction [8, 37–39]. According to our unpublished data, DE during deep breathing of 4 cm or less could also indicate diaphragmatic dysfunction. In this trial, PORC will be defined as TF ≤ 0.36 or DE ≤ 4cm.

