#### Exclusion criteria

The following are the exclusion criteria:Those with a history of hepatic or renal disease, chronic or acute alcoholism, allergy or hypersensitivity to sugammadex or neostigmine, current medication with effects on the central nervous system, and a history of dysfunction of the neuromuscular system.Those with diaphragm insufficiency (which can be determined by maximal inspiratory pressures and phrenic nerve stimulation) or massive pleural effusion.Those undergoing upper abdominal laparotomy will be excluded, after which we cannot obtain a satisfactory ultrasound imaging or do not have space for placement of the ultrasonic probe.Those who are extremely old and frail (which can be determined by the FRAIL Scale) and need adjustment of drug dosage.

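### PORC is defined by post-extubation cut-offs alone, so a diaphragm already low before induction counts as residual curarization in either arm and attenuates the comparison by an unknown amount

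*Protocol article*

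**What the plan says.** The Secondary endpoints section of the protocol article names the outcome as "the incidence of PORC in the two groups 10 min and 30 min after extubation, using diaphragmatic ultrasound as the method of appraisal". It then fixes the rule: "In this trial, PORC will be defined as TF ≤ 0.36 or DE ≤ 4cm". Meeting either criterion is enough, and the patient's own earlier value plays no part. The section presents both cut-offs as indicators of diaphragm dysfunction in general, not of a change caused by the relaxant.

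The Diaphragm ultrasonography section schedules three scans: "Before induction of anesthesia, 10 min after extubation, and 30 min after extubation, the right hemidiaphragm of the patient will be evaluated". The baseline value is therefore planned for every patient.

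The Exclusion criteria remove "Those with diaphragm insufficiency (which can be determined by maximal inspiratory pressures and phrenic nerve stimulation) or massive pleural effusion". They do not mention TF or DE.

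The Statistical analyses section names a χ² test for dichotomous data and a paired t-test for comparing the same index. No size, rate or power is stated for PORC.

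**The concern.** Residual curarization is an effect of the relaxant that persists. A rule based only on the value after extubation cannot separate that effect from a diaphragm that was low before any relaxant was given. The trial enrols patients over 60, and nothing in eligibility requires them to start above 0.36 and 4 cm.

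The distinction matters for the trial's own argument. The TOF monitoring section notes that "TOFr > 0.9 is one of the extubation standards", and the stated aim is to show that diaphragm recovery may be incomplete although the peripheral ratio is adequate. Every PORC call is thus made in a patient whom the peripheral monitor regards as recovered, and recovery of the diaphragm can be judged only against where it started. What is at stake is an overstated PORC incidence in both arms and a muted contrast on the secondary endpoint.

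**Working it through.** **The plan's own figure.** The 207 per group is sized on PPC, not PORC. Taking 15.4% vs 5% (the use of 5% as the sugammadex rate is inferred), two-sided α 0.05, power 90% and unpooled variance gives 172.7 per group, and 172.7 × 1.2 = 207.3. It reproduces on those inputs. Here it serves only as the available number per arm.

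**Inputs for PORC**
- n = 207 per arm, allocation 1:1, α = 0.05 (two-sided is an assumption).
- b, the share of each arm below a cut-off at baseline and again after extubation: not in the documents, varied from 0 to 30%.
- True new-onset rates p(NEO) and p(SUG) under this rule: not in the documents, assumed.

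**Model.** Baseline-low patients are positive in both arms, so

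observed rate = b + (1−b)·p, and observed risk difference = (1−b)·[p(NEO) − p(SUG)].

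**Power.** With d the difference, p̄ the mean of the two rates, and p1, p2 the rates:

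Power = Φ[(d − 1.96·SE0)/SE1], SE0 = √(2p̄(1−p̄)/n), SE1 = √([p1(1−p1) + p2(1−p2)]/n).

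**Worked case: b = 20%, true rates 30% vs 15%**
- As written: 0.20 + 0.80×0.30 = 0.44 and 0.20 + 0.80×0.15 = 0.32. The difference is 0.12 instead of 0.15, and the risk ratio is 0.73 instead of 0.50. SE0 = √(2×0.38×0.62/207) = 0.0477 and SE1 = √((0.2464+0.2176)/207) = 0.0473. Power = Φ[(0.12 − 0.0935)/0.0473] = 71%.
- New crossings only: n = 207×0.80, rounded down to 165 per arm, with rates 0.30 vs 0.15. SE0 = 0.0460 and SE1 = 0.0452. Power = Φ[(0.15 − 0.0901)/0.0452] = 91%.

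**Range, assumed 30% vs 15%**

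| b | Observed rates | Risk difference | Risk ratio | Power as written | n per arm, new crossings | Power, new crossings |
|---|---|---|---|---|---|---|
| 0 | 30.0% vs 15.0% | 15.0 points | 0.50 | 96% | 207 | 96% |
| 5% | 33.5% vs 19.3% | 14.2 points | 0.57 | 91% | 196 | 95% |
| 10% | 37.0% vs 23.5% | 13.5 points | 0.64 | 85% | 186 | 94% |
| 20% | 44.0% vs 32.0% | 12.0 points | 0.73 | 71% | 165 | 91% |
| 30% | 51.0% vs 40.5% | 10.5 points | 0.79 | 57% | 144 | 87% |

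**Other assumed effects**
- 45.2% vs 30% (45.2% is the PACU figure in the Background, not given for this ultrasound rule): 89% at b=0. As written, 80%, 70% and 59% at b = 10%, 20% and 30%; with new crossings, 86%, 82% and 76%.
- 45% vs 15%: still 99% as written at b = 30%.

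**Imperfect persistence.** If only 70% of baseline-low patients stay low and the rest are negative in both arms, power for 30% vs 15% is 87%, 75% and 60% at b = 10%, 20% and 30%. The direction is unchanged.

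**The case against.** The strongest reply is that the quantity driving the harm is unknown. No section gives b, and eligibility probably lowers it: diaphragm insufficiency, neuromuscular dysfunction, massive pleural effusion and extreme age with frailty are all excluded. At b = 2% the assumed 30% vs 15% case has 94% power as written against 95% with new crossings. No PORC power is promised, so none is breached. This stands: the loss is conditional and small when b is 5% or less. The exclusions narrow the gap without closing it, because none refers to TF or DE. The wording that insufficiency is something "which can be determined by maximal inspiratory pressures and phrenic nerve stimulation" is permissive, so it also cannot be said that a given patient with a low baseline scan would certainly be enrolled.

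A second reply is that baseline scans are used elsewhere: the abstract lists the pre-anaesthesia scan among the secondary evaluations, and a paired t-test is planned. That is true, but neither alters the binary PORC call.

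Several stronger readings are tempting and are not supported:
- **Bias toward one drug.** Baseline status precedes treatment and randomisation balances it in expectation. The effect is attenuation; the type I error rate is not affected.
- **Misuse of a rule-out value.** The text says "TF during a deep breath of 0.36 was considered as the threshold to exclude diaphragm dysfunction", but this may simply mean the value separating normal from abnormal. One verb cannot settle it without the cited sources.
- **A wrong DE cut-off.** "According to our unpublished data, DE during deep breathing of 4 cm or less could also indicate diaphragmatic dysfunction" limits verification; it does not show that 4 cm is wrong.
- **Harm from joining the criteria with 'or'.** A union rule also raises sensitivity. No sensitivity or specificity is given, so the net effect is unknown.

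**Conclusion.** The point holds in a limited form. The definition is stated in full and contains no baseline reference, although the information needed is already collected. It can therefore count pre-existing low diaphragm function as residual curarization in both arms and shrink the risk difference by about (1−b). The size cannot be known from the documents: under the assumed rates it runs from negligible (small b, or a large true effect) to a fall from 96% to 57% power (30% vs 15%, b = 30%). The figures assume equal b in the arms, persistence of low values in baseline-low patients, and two-sided testing at 207 per arm. This is a worthwhile correction to a secondary endpoint. It is no threat to the validity of the trial.

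**What to change.** Before the first unblinding step, amend the definition and its analysis:
1. Define PORC as new onset: TF above 0.36 and DE above 4 cm before induction, with TF or DE at or below its cut-off at the 10 or 30 min scan. Analyse it in patients above both cut-offs at baseline. This subset is fixed before treatment, so the randomised comparison within it is preserved.
2. Report by arm the proportion below each cut-off at baseline. This shows directly how large b was.
3. Keep the present absolute rule in all patients as a sensitivity analysis, supported by a between-arm comparison of post-extubation TF and DE adjusted for the baseline value, also in all patients.

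The cost is wording and analysis only; no new measurement is needed. There are two real drawbacks. Patients low at baseline leave the binary endpoint, which narrows the population it describes in a trial aimed at vulnerable older patients. Values just above a cut-off can also cross it through measurement noise, which the new-crossing power figures ignore. The all-patient analyses in step 3 are there to cover both. If b proves close to zero, the results will barely change.
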